The multiple baseline design is ideal because it enables more valid causal inferences by staggering the intervention sequentially across one clinician at a time [46]. Consistent with the single-case intervention research design standards [46], the introduction of and training in the implementation strategy toolkit will be staggered across EI clinicians within agencies. The implementation strategy toolkit will be introduced with each subsequent clinician when the preceding clinician attains at least 80% coaching fidelity or fidelity stabilizes across three sessions, until the toolkit has been introduced across all three clinicians within each agency. The same procedure will be used for all three agencies. Three clinicians per agency will allow for an adequate demonstration of phase repetitions to infer causal relationships between the independent and dependent variables [46]. Progression through the phases of the multiple baseline design is dependent upon the change in EI clinicians’ parent coaching fidelity. We will visually analyze the data independently along two dimensions: (1) within phases—to evaluate level, trend, and variability of the data points and (2) across phases—to evaluate immediacy of effect, overlap, and consistency of data in similar phases. This will allow us to assess whether there are at least three demonstrations of effect across three different points in time and make causal inferences about any observed changes in EI clinician parent coaching fidelity [46]. The primary outcome of interest is EI clinician fidelity to the Project ImPACT Fidelity of Implementation for Coaching Form, as this outcome is most proximally related to the implementation strategy toolkit. Progression through the multiple baseline design phases will be contingent upon changes in provider coaching fidelity. In the event that a provider does not attain 80% coaching fidelity after the toolkit is introduced, a contingency plan consistent with best practices in single-case intervention research design standards will be adopted [47]. Each provider’s coaching fidelity data will be graphed and visually analyzed following each session to evaluate level, trend, and variability of the data points. If these analyses indicate that a provider’s coaching fidelity is (1) stable and (2) not demonstrating an increasing trend over three consecutive sessions, the implementation toolkit will be introduced with the subsequent provider in the multiple baseline design, while continuing to intervene and monitor coaching fidelity with the previous provider. Secondary outcomes include changes in parent’s use of the treatment strategies and children’s social communication. These secondary outcomes will be recorded and analyzed prior to and following the intervention to evaluate changes in either of these distal outcomes as a function of the introduction of the implementation strategy toolkit.

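### The 80% limb of the progression rule is met by one session and no minimum gap between starts is set, so an abrupt toolkit effect shortens the stagger to its minimum

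*Protocol article*

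**What the plan says.** Under Design and analysis, the protocol article has the toolkit "introduced with each subsequent clinician when the preceding clinician attains at least 80% coaching fidelity" or, in a second limb of the same sentence, when that clinician's fidelity has stabilised over three sessions. This continues "until the toolkit has been introduced across all three clinicians within each agency". A contingency follows. It opens "In the event that a provider does not attain 80% coaching fidelity after the toolkit is introduced" and moves on to the next provider once the current one is "stable and (2) not demonstrating an increasing trend over three consecutive sessions", while intervention and monitoring continue for the provider who fell short.

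The same section rests its causal claim on the stagger, saying of the design that "it enables more valid causal inferences by staggering the intervention sequentially across one clinician at a time". The evidence standard is "at least three demonstrations of effect across three different points in time", and the comparison across phases is "to evaluate immediacy of effect, overlap, and consistency of data in similar phases".

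Elsewhere, Phase 4 Participants gives nine clinicians, three per agency. Phase 4 Measures has coaching fidelity rated at each session. The Project ImPACT section describes the sessions as weekly.

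**The concern.** The two limbs ask for different amounts of evidence. A clinician who does not reach 80% must show three consecutive stable sessions before the next one starts. A clinician who does reach 80% needs, as written, one session. Neither mention of 80% carries a duration.

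In a multiple-baseline design, control comes from the sessions in which one clinician already has the toolkit and the next is still in baseline. The faster the first clinician responds, the fewer such sessions this rule leaves. An immediate response is also one of the features the visual analysis looks for, so the rule gives the weakest control in that case. At each decision the preceding clinician may have one toolkit data point, which shows neither trend nor variability. A stagger lost during conduct cannot be restored in the analysis.

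**Working it through.** The plan gives no figure for the expected gap between starts, so there is none to reproduce. The check asks how long the gap would be under the rule as written.

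**From the document:** 80% criterion without a session count; three sessions for the stability limb; three clinicians per agency, hence two gaps; fidelity scored every session; weekly sessions.

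**Assumed, because the document does not give them:** session scores vary normally around the clinician's level with SD 8 or 10 points; level after the toolkit 85% or 90%; for gradual uptake, a baseline of 45% rising in equal steps over three or six sessions; stable means a range of at most 10 points over three sessions with no rise from first to third.

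**1. Abrupt effect.** Let p be the probability that a toolkit session scores at least 80%: p = Φ((level − 80)/SD). The gap is one session with probability p, and both gaps in an agency are one session with probability p².

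| Level | SD | p | p² |
|---|---|---|---|
| 85 | 10 | Φ(0.5) = 0.69 | 0.48 |
| 85 | 8 | Φ(0.625) = 0.73 | 0.54 |
| 90 | 10 | Φ(1.0) = 0.84 | 0.71 |
| 90 | 8 | Φ(1.25) = 0.89 | 0.80 |

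Starts then fall at sessions 0, 1 and 2, a span of about two weeks, with one session of overlap between neighbouring clinicians.

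**2. Gradual uptake.** Simulation of both limbs together, SD 8:

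| Level reached | Sessions to reach it | Mean gap | P(gap = 1) |
|---|---|---|---|
| 90 | 1 (abrupt) | 1.1 | 0.90 |
| 90 | 3 | 2.8 | 0.006 |
| 85 | 3 | 3.1 | 0.003 |
| 90 | 6 | 4.7 | about 0 |

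The one-session gap is therefore a feature of abrupt response only.

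**3. A chance high score.** A clinician whose true level is 70% scores at least 80% in a given session with probability 1 − Φ(10/8) = 0.11 (SD 8) or 1 − Φ(10/10) = 0.16 (SD 10). One such session meets the 80% limb.

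**4. Effect of a three-session rule.** The minimum gap becomes 3 sessions instead of 1, and the minimum span from first to third start 6 instead of 2. If the mean of three sessions is used, the chance that the first three toolkit sessions meet it is Φ((level − 80)/(SD/√3)): 0.81 and 0.86 at level 85 (SD 10, 8), and 0.96 and 0.98 at level 90. Requiring each of the three to reach 80% is stricter: at level 85 it gives 0.69³ = 0.33 and 0.73³ = 0.39.

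**The case against.** **Wording.** The three-session phrase could be read as covering both limbs. The second mention of 80%, again without a duration, and a contingency confined to those who fall short both favour the literal reading. An article may also leave operational detail to a full protocol. This one, however, states the rule and gives a session count for one limb only.

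**Gradual uptake.** The candidate strategies (extra training, guided practice, handouts, text messages) may well act slowly, and then the gaps are adequate. This stands and limits the point to an abrupt response.

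**Replication.** The sequence is run in three agencies, and an event inside one agency does not explain changes in the other two. This also stands. The protection is partial, because the article does not say that the agencies start at different times, so a system-wide event is not excluded.

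**Stronger readings to avoid.** A reader might infer that the stagger collapses whenever the toolkit works. It does not: starts stay at least one session apart and three different time points are formally kept.

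A reader might also combine the 48-80% above with an example of a false effect. Take a 15-point agency-wide rise at the first start, no toolkit effect and five baseline sessions. With e raised baseline sessions the apparent change is 15 × 5/(5 + e), which is 15.0, 12.5 and 10.7 points for e = 0, 1, 2. But without a toolkit effect, one-session gaps need the rise itself to reach 80%. From a baseline of 45% the level becomes 60%, p is 0.006-0.023 and p² is below 0.1%. From 60%, p² is about 7-10%. Only a baseline near 70% brings it back to 48-54%. The article gives no baseline level and describes coaching as rare. The planned visual analysis also looks at immediacy and overlap, not only at differences in phase means.

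Finally, a clinician truly at 70% (SD 10) would score 80% at least once in six sessions with probability 1 − (1 − 0.159)⁶ = 0.65. That figure ignores the stability limb, which may legitimately start the next clinician first.

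**Conclusion.** The point holds in a limited form. As written, one session at 80% starts the next clinician and nothing sets a minimum gap. For an abrupt effect to 85-90% with session SD 8-10, both gaps in an agency are one session in about 48-80% of agencies. In such an agency each decision rests on one toolkit data point, and an agency-wide event within about two weeks is hard to tell from the toolkit effect. For uptake over three to six sessions the mean gap is about 3-5 sessions and little remains of the problem. The level, SD and speed of uptake are assumptions; the article gives none of them.

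The documents do not support saying that the causal inference fails. The rule allows weaker control than a small change of wording would secure. Because Phase 4 is a nine-clinician pilot meant to give preliminary evidence before a randomised trial, this is something to fix but not critical.

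**What to change.** Reword the progression rule so that the next clinician starts when the preceding clinician either is at or above 80% over three consecutive toolkit sessions (for example, by their mean) or is stable without an increasing trend over three consecutive sessions. Add that consecutive starts within an agency are never fewer than three toolkit sessions apart. State that the continued monitoring already planned for providers who do not reach 80% also applies to those who do.

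**Cost.** In the fastest case each step takes two more sessions, (3 − 1) × 2 = 4 more weekly sessions before the third clinician starts. A simulation of the mean-based rule under the assumptions above gives about 3.7-3.8 added sessions over both steps for an abrupt effect to 85-90%, and about 2.3-3.0 for uptake over three to six sessions. For clinicians who level off well below 80% the wait can be longer, because a single high score no longer ends it; how much longer depends on how stability is defined.

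The added sessions must fit the child's remaining time in the service. Children enter below 30 months and leave at 36 months, so at least six months, or about 26 weeks (6 × 52/12), are available at enrolment.

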
## Discussion

Several models of parent-mediated interventions for young children with ASD have been shown to improve child and parent outcomes [1–5]. Each of these models includes the use of parent coaching to actively transfer skills from a clinician to the parent. However, preliminary evidence suggests that clinicians working in community settings rarely adopt parent coaching techniques with families of young children with ASD. This study will use a community-partnered iterative process to develop and pilot test a toolkit of implementation strategies to improve EI clinicians’ use of parent coaching for families of young children with ASD in community settings. Completion of the activities in this pilot study will lead to (1) an in-depth understanding of EI clinicians’ implementation of parent coaching in usual practice following training in an evidence-based parent-mediated intervention; (2) barriers to their implementation of parent coaching; (3) a toolkit of implementation strategies developed through an iterative community-partnered process; and (4) preliminary evidence regarding the potential for this toolkit to improve EI clinicians’ implementation of parent coaching. These research findings will lay the foundation for a later proposal to test the effectiveness of the toolkit in a randomized trial.

The implementation strategies developed through this study will be contextually relevant to the Philadelphia EI setting and tailored to each individual clinicians’ needs. For example, implementation strategies for a clinician with poor use of parent coaching due to poor attitudes toward coaching (i.e., prefers a more child-directed approach to treatment) may include infographics describing the benefits of parent coaching or exposure to vignettes of other clinicians reporting favorable views toward parent coaching. Conversely, implementation strategies for a clinician with poor use of parent coaching due to poor self-efficacy may include additional guided practice and feedback. This individualized approach to selecting implementation strategies for each clinician is likely to improve the effectiveness of the implementation toolkit and offers important insights into the feasibility of individualizing implementation strategies for clinicians within a larger system. Future research should expand upon this line of work and include an in-depth examination of organizational and system-level barriers to implementing parent coaching within early intervention and developing implementation strategies to address those barriers.

## Conclusions

The study described in this paper encompasses several important innovations for the implementation of evidence-based treatment models for young children with ASD in community settings. First, this study is the first to study the use of parent coaching strategies for young children with ASD in community settings, rather than autism interventions per se, which is important because parent coaching is likely the active mechanism of change within parent-mediated interventions. Tools developed to support the use of parent coaching can likely be applied to many intervention models and improve the implementation of community-based autism treatment more broadly. Second, despite growing evidence to support the use of parent-mediated interventions for young children with ASD, little attention has been given to the actual use, and barriers and facilitators to using these approaches, within community-based treatment setttings. This study will provide important insights into the challenges of implementing evidence-based treatments for young children with ASD in community settings and potential strategies to overcome these challenges. Finally, this research study relies heavily on a partnership with the EI system and uses iterative community-partnered research methods to inform the approach throughout all phases of the project. This community-partnered approach will improve the ecological validity of the strategies developed through this study and will ensure that they are consistent with the community’s needs and priorities [24, 25]. The study described in this paper provides valuable insights into strategies to support the implementation of evidence-based practices for young children with ASD in community settings.

## Data Availability

Not applicable

## Abbreviations

EI: Early intervention
ASD: Autism spectrum disorder
